#### Design:

[figure not shown]

Participants will enter a screening period, which includes Visit 1 and if necessary a medication washout period.

Subjects who are deemed eligible after this screening period will return for a baseline evaluation (Visit 2), including clinical evaluation and mucosal specimen collection, as well as the Baseline Behavioral Questionnaire (BBQ). The BBQ will be administered by Computer Assisted Self-Interview (CASI). Subjects may complete the web-based CASI in the privacy of their own home. If a subject does not have access to the Internet, prefers to complete the BBQ at the study site, or requires assistance in using the CASI, he or she will be accommodated at the study site.

After completing Visits 1 and 2, eligible subjects will be randomized to one of three groups: 0.1% UC-781 gel, 0.25% UC-781 gel, or a placebo gel (12 per group). A subset of 9 subjects (3 from each group) will also participate in a pK sub-study, which will include 6 timepoints (Visit 3-pre, 0.25 hr, 2 hr, 4 hr, Visit 3A- 24 hr, and Visit 5- 1 day post-QD dose). During randomization, study staff will be notified if the participant is randomized to the pK substudy.

This study will involve 2 stages of treatment. **Each treatment stage is independent of the other. This study aims to examine the effects of 2 different dosing regimens, NOT cumulative safety over the both stages.**

Once randomized, subjects will return to the clinic (Visit 3), where a single dose of the study gel (Treatment Stage 1) will be administered after a preparatory Normosol-R pH7.4 enema. Within approximately 30 minutes, lavage, stool, sponge, and colorectal biopsy specimens will be obtained. Subjects will receive a safety follow-up phone call.

Subjects will return to the clinic for Treatment Stage 2 Clearance (Visit 4), in the week prior to beginning Treatment Stage 2. If given clearance, the subject may begin Treatment Stage 2.

In Treatment Stage 2, subjects will begin to self-administer once daily outpatient doses of the study gel for 7 days. Subjects will receive a follow-up safety phone call mid-way through

Stage 2. After completion of Stage 2 the subject will complete a Product Acceptability Questionnaire (PAQ) by CASI and return to clinic for evaluation and specimen collection (Visit 5). Subjects will receive a safety follow-up phone call.

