Participants' plasma samples were analyzed for UC-781 at baseline and after 6 applications of placebo gel, 0.1%, 0.25%, or 1% UC-781 gel. The lower limit of quantification (LLOQ) of the LC-MS bioanalytical assay was 2.5 ng/mL. There were no detectable levels of UC-781 in samples after treatment with placebo gel or 0.1% and 0.25% UC-781 gels. After six daily applications, two participants who were randomized to the 1% UC-781 gel group had plasma levels that were detectable but less than the LLOQ.

The key acceptability item was whether or not the subject indicated that she would buy the product if she needed protection against HIV and if the product she used were effective. All of the participants indicated that they would buy the product if proved effective with only one exception in the 0.1% UC-781 group.

Another Phase I study conducted at Emory University was started in October 2005 in order to assess the safety and acceptability of vaginal use of 0.1% and 0.25% UC-781 gel in sexually active HIV-uninfected women, and their male partners, and sexually abstinent HIV-infected women. The population will consist of 36 sexually active HIV-uninfected women and up to 36 of their male partners; in addition to 18 sexually abstinent HIV-infected women

The study will proceed in two stages. In Stage 1, sexually active HIV-uninfected women will be randomized to apply 0.1% UC-781 Gel, 0.25% UC-781 Gel or Control Gel intravaginally twice daily for 14 days. If safety data from stage 1 is acceptable with no evidence of UC-781 systemic absorption, the study will proceed to Stage 2. In Stage 2, sexually abstinent HIV-infected women will be randomized to apply 0.25% UC-781 Gel or Control Gel intravaginally twice daily for 14 days.

This Phase I study will continue the clinical development pathway for UC-781, progressing from the initial 6-day study of multiple concentrations in sexually abstinent women to a 14 day, twice daily application study using 0.1% and 0.25% concentrations in sexually active women. Because, the potential for absorption is higher with the 1% formulation, this 14-day study will involve the 0.1% and 0.25% UC-781 gel formulations only.

Recruitment is anticipated to take 6 months. Currently, there are 3 subjects enrolled into the trial. No serious adverse events have been reported.

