## 2.2 Study Design

This is a phase I randomized, blinded, placebo-controlled study of the safety and acceptability of the vaginal formulation of UC-781 gel, when administered rectally, to be conducted in 36 adults (12 per group) residing in the Los Angeles, CA area. All of the participants will be HIV negative. The study design is summarized in the Schema above and the Schedule of Events in Appendix I.

This study will involve 2 stages of treatment. Each treatment stage is independent of the other. **This study aims to examine the effects of 2 different dosing regimens, NOT cumulative toxicity over both stages.** Participants will undergo extensive evaluation during 5 study visits over an approximately 7-14 week period. In addition, acceptability assessments will be completed at baseline and Visit 5.

Interested participants will enter a screening period, which includes (Visit 1) and if necessary a medication washout period. Subjects, who are deemed eligible after this screening period, will return for a baseline evaluation (Visit 2), including clinical evaluation and mucosal specimen collection, as well as a baseline behavioral assessment (BBQ). The BBQ questionnaire will be administered by CASI. Subjects may complete the web-based CASI in the privacy of their own home. If a subject does not have access to the internet, prefers to complete the BBQ at the study site, or requires assistance in using the CASI, they will be accommodated at the study site.

After completing Visits 1 and 2, eligible subjects will be randomized to one of three groups: 0.1% UC-781 gel, 0.25% UC-781 gel, or a placebo gel (12 per group). A subset of 9 subjects (3 from each group) will also participate in a pK sub-study, which will include 6 timepoints (Visit 3- pre, 0.25 hr, 2 hr, 4 hr, Visit 3A- 24 hr, and Visit 5- 1 day post-QD dose draw). During randomization, study staff will be notified if the participant is randomized to the pK sub-study. Subjects will be randomized in blocks of 3, one per group to minimize imbalance in treatment assignments. The first three subjects enrolled in each of three treatment groups will be selected for the pK sub-study. It is possible that participants may refuse to participate in the sub-study, and spots will continue to be offered as needed.

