### 5.3.2 Clinical Procedures

**NOTE: During this visit the timepoints listed below are approximate. Every effort will be made to adhere to the timeline, however due to logistics timing will not be exact. However, the sequence of sample collection during the following visits is crucial.**

- ⊙ Interval medical history\*, including AE assessment, will be collected to assure continued healthy status and safety of study interventions.
 

*\* Note for female participants this includes notation of the LMP.*
- ⊙ Basic physical examination as defined in section 5.1.2
 

*(If participant has peri-anal or rectal HSV lesions, referrals for treatment will be provided and Visit 3 will be postponed until outbreak resolved.)*
- ⊙ **If female of child-bearing potential, collect urine for STAT HCG testing**
- ⊙ Collect blood specimens, including pre-dose pK draw if applicable
- ⊙ Collect rectal swabs and sponge specimens

- ⊙ Administer preparatory Normosol-R pH7.4 enema
- ⊙ Collect stool specimen
- ⊙ T=0 Administration of single-dose of study gel by study staff  

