## 5.7 Visit 5 – (Week 6 +/- 2 weeks) Treatment 2 Follow-up

*Although time from Week 0 may vary by several weeks, visit must be scheduled for Day 8 of Treatment Stage 2 (the day following the last dose of study product +/- 1 day).*

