### 5.7.3 Laboratory Procedures

- ⊙ Safety Labs as defined in section 5.1.3
- ⊙ STD screen as defined in section 5.1.3
- ⊙ Research panel
  - Epithelial sloughing assay (Lavage)
  - Histopathology (~1 biopsy)
  - Microflora (~1 rectal swab)
  - Mucosal mononuclear cell phenotype (~4 biopsies)
  - Mucosal cytokine profile (~3 biopsies)
  - Immunoglobulin assay (~ 2 rectal sponges)
  - Fecal calprotectin assay (Stool)
  - Explants studies (~6 biopsies, ~10ml blood)
  - UC-781 blood level for sub-study participants (~5ml)

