## **7.9 Statistical Procedures for Analysis of Pharmacokinetic Data**

Pharmacokinetics of UC-781 will be evaluated after rectal administration. This will include the UC-781 pK profile of the initial dose (Visit 3) and UC-781 1 day post-QD dose level (Visit 5). The analysis will be performed by investigating plasma concentrations of UC-781 and determining the AUC. Possible UC-781 accumulation will be determined by comparing the median UC-781 AUC on Visit 5 to the median AUC on Visit 3. Maximum concentration of drug ( $C_{max}$ ) and time to reach maximum concentration of drug ( $T_{max}$ ) will be calculated as part of the analysis as stated above.

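### Section 7.9 judges UC-781 accumulation by an AUC at Visit 5, but the schedule takes one blood sample there, so that AUC cannot be calculated

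*Protocol*

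**What the plan says.** Section 2.2 sets the sampling for the sub-study of 9 participants, 3 per group: "6 timepoints (Visit 3- pre, 0.25 hr, 2 hr, 4 hr, Visit 3A- 24 hr, and Visit 5- 1 day post-QD dose draw". The Schema gives the same list and ends it in the same way: "Visit 3A- 24 hr, and Visit 5- 1 day post-QD dose".

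The visit procedures agree. Section 5.3.2 has a pre-dose sample ("Collect blood specimens, including pre-dose pK draw if applicable"), then draws at 15 min, 2 h and 4 h, and at 24 h on Visit 3A. Section 5.3.3 allots about 25 ml of blood to these. For Visit 5, section 5.7.3 has "UC-781 blood level for sub-study participants (~5ml". Neither section 5.7.2 nor section 5.7.3 lists a gel dose or a timed series at that visit. Section 5.7 places Visit 5 on "the day following the last dose of study product +/- 1 day".

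Section 7.9 first describes the Visit 3 data as a profile and the Visit 5 measurement as a level. It then sets the accumulation analysis: "Possible UC-781 accumulation will be determined by comparing the median UC-781 AUC on Visit 5 to the median AUC on Visit 3".

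**The concern.** An AUC needs concentrations at two or more times. Section 7.9 asks for one at a visit where a single concentration is measured, so it contradicts both the schedule and its own description of the Visit 5 measurement. No other accumulation analysis is given.

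If the text stands, whoever analyses the data must either drop the comparison or devise a Visit 5 AUC after seeing the results. Section 2.1.3 justifies the blood levels as an indication of resistance risk before later trials that may include HIV-positive participants. Whether levels build up over a week of daily use bears on that question, so the substitute should be chosen in advance.

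**Working it through.** **Count of samples.** Sections 2.2 and 5.3.2 give Visit 3/3A samples at 0 (pre-dose), 0.25, 2, 4 and 24 h, which is 5. The stated total is 6, leaving 6 − 5 = 1 for Visit 5. The blood volumes confirm this: 25 ml / 5 draws = 5 ml per draw at Visit 3, and 5 ml / 5 ml = 1 draw at Visit 5.

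**What an AUC needs.** The trapezoidal rule on n samples has n − 1 intervals. Visit 3/3A has 5 − 1 = 4, so AUC(0-24) can be calculated. Visit 5 has 1 − 1 = 0, so it cannot.

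**Could one level stand in for the AUC?** Only with a model. The protocol gives no half-life, so the following is an illustration that assumes mono-exponential decline from the time of dosing. With k = ln 2 / half-life and a 24 h level of 1 unit, AUC(0-24) = (e^(24k) − 1) / k:

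| Assumed half-life (h) | AUC(0-24), unit·h |
|---|---|
| 4 | 363.6 |
| 8 | 80.8 |
| 12 | 51.9 |
| 24 | 34.6 |
| 48 | 28.7 |

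The same level fits AUCs that differ by 363.6 / 28.7, about 13-fold. If k were borrowed from Visit 3 and the same formula used at both visits, the factor (e^(24k) − 1) / k would cancel. The AUC comparison would then reduce to comparing the two 24 h levels.

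**How comparable are the two levels?** The one quantity measured at both visits is the concentration about a day after a dose: Visit 3A and Visit 5. Two features loosen the pairing.

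First, the one-day tolerance on Visit 5. Under the same assumption, accumulation of the 24 h level after 7 daily doses is (1 − e^(−7·24k)) / (1 − e^(−24k)), and sampling 24 h early or late changes the concentration by 2^(24/half-life):

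| Assumed half-life (h) | Accumulation, 7 doses | Effect of a 24 h shift |
|---|---|---|
| 12 | 1.33 | 4.0-fold |
| 24 | 1.98 | 2.0-fold |
| 48 | 3.11 | 1.41-fold |

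Second, the procedures. At Visit 3 the lavage and 14 + 14 = 28 biopsies come at about 30 min (section 5.3.2), so the 24 h sample follows them. At Visit 5 blood collection is listed ahead of the enema and sigmoidoscopy (section 5.7.2).

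**The case against.** The strongest reply is about weight. The objective is tertiary, and sections 2.1.3 and 7.9 between them mention accumulation in a single sentence, in 7.9. The parameter named in 2.1.3 is blood levels to determine absorption, and every scheduled level, including the one at Visit 5, is still drawn and analysed. No sample size, safety decision, or primary or secondary result depends on the AUC comparison. All of this stands and limits the importance of the point. It does not make the sentence workable.

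A second reply is that an analysis plan, not seen here, may define the pharmacokinetic calculations. It could set a rule for computing an AUC or adopt another comparison. It cannot create Visit 5 samples, so an AUC there would rest on a model that the protocol does not state.

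A reader might also draw stronger conclusions that the protocol does not support:

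- **That the visit window swamps any accumulation.** This depends on the unknown half-life. In the illustration the window effect exceeds accumulation at 12 h and is about equal to it at 24 h. At 48 h accumulation is clearly larger (3.11 against 1.41).
- **That the comparison fails because a ratio of medians would be undefined.** Section 7.9 speaks of comparing medians and specifies no ratio. The vaginal study in section 1.2.3 did report that "There were no detectable levels of UC-781 in samples after treatment with placebo gel or 0.1% and 0.25% UC-781 gels" (LLOQ 2.5 ng/mL). Vaginal data are a weak guide to rectal absorption, though, since section 1.1 describes the rectal lining as more likely to allow systemic exposure. Unquantifiable levels are possible, not established.
- **That the Product Use Log omits dose times.** Section 4.6 mentions the date of each dose, but only in summary. The sample log in Appendix IX is not in the text available, so this cannot be shown.

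**Conclusion.** The contradiction is certain and rests on a count: five samples at Visit 3/3A, one at Visit 5, and no AUC from one sample. The accumulation analysis in section 7.9 cannot be done as written and should be corrected.

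Its reach is small. It concerns one analysis under a tertiary objective, in 9 participants of whom 6 receive active gel (3 per active arm). It would be wrong to infer that the pharmacokinetic objective as a whole is lost. Absorption can still be described from all six levels, and AUC, Cmax and Tmax can still be calculated for the first dose; 7.9 does not assign Cmax or Tmax to Visit 5.

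The half-life figures assume mono-exponential decline with no absorption phase. They show that the timing of the Visit 5 sample can matter. The main conclusion does not depend on them.

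**What to change.** Reword section 7.9 to:

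1. Limit AUC(0-24), Cmax and Tmax to Visits 3 and 3A.
2. Replace the AUC comparison with a descriptive, within-participant comparison of the Visit 5 level with the Visit 3A 24 h level.
3. List individual values with the actual time since the last dose, and give the number above the LLOQ by arm and time point. Give a ratio only where both values are quantifiable, since two levels taken about a day after dosing may well fall below the limit.
4. State two limitations. The one-day tolerance means Visit 5 is not a fixed 24 h level, and recording the time does not correct for this without a known half-life. The Visit 3A sample follows lavage and biopsy.

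The cost is a change of wording in 7.9 and making sure that the time of the last dose is recorded. No new samples are needed. Keeping a true AUC comparison would instead require several timed samples over a dosing interval in Stage 2, which the present schedule does not contain.

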## **7.10 Statistical Procedures for Missing Data**

All reasonable efforts will be made to obtain complete data for all patients; however, missing observations will occur due to missed visits, patients lost to follow-up, or noncompliance with the full acceptability assessment or secondary measures. In order to account for this, and to be able to perform intent to treat analysis on the outcomes, multiple imputation will be employed. The imputation will be implemented using the MI procedure in SAS or the IveWARE library. In order to construct these models independently of the data from the current study, imputation model building will be based wherever possible on the data from HPTN 056.

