#### PRN visits

- Any complications that arise may require further clinical evaluation.

**Study Population:** HIV negative men and women with a history of RAI \*

*\*Refers to coitus only, does not include manual stimulation or the use of sex toys or purgatives.*

**Study Size:** A total of 36 participants (12 per treatment group).  
A subset of 9 participants will be assigned to the pK study.

|                           |                                                |            |
|---------------------------|------------------------------------------------|------------|
| Treatment Regimen: | Treatment Stage 1- Study gel administered once | Clinic     |
|                           | Full 7-day recovery period                     |            |
|                           | Up to 3 weeks later:                    |            |
|                           | Treatment Stage 2- Study gel QD x 7 days       | Outpatient |

**Study Duration:** Participant accrual will take approximately 9-12 months and each participant will be on study for approximately 7-14 weeks. The total duration of the study will be approximately 18 months. Specimen and data analysis will require an additional four months.

**Primary Objective:** To evaluate the safety and acceptability of 0.1% and 0.25% UC-781 vaginal microbicide gel versus placebo when applied rectally.

Parameters to be studied include: Frequency of  $\geq$  Grade 2 adverse events  
Acceptability assessments

**Secondary Objective:** To determine whether use of study product is associated with rectal mucosal damage characterized by the following:

Parameters to be studied include: Epithelial sloughing  
Histopathology  
Microflora  
Mucosal mononuclear cell phenotype  
Mucosal cytokine profile  
Mucosal immunoglobulins  
Fecal calprotectin  
Explants- Mucosal cytokine profile and susceptibility to HIV infection

**Tertiary Objective:** To determine the pharmacokinetics of UC-781 vaginal microbicide gel administered rectally in a subset of participants.

Parameters to be studied include:  
UC-781 blood levels to determine absorption from the GI tract

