### Developing Safety Standards for Rectally-Administered Microbicides

Methods of assessing mucosal parameters characterizing any insult to the rectal mucosa that might guide the development of future rectal microbicides have not been established. Many safety risks may be subtle and require alternate modes of detection (PCR, flow cytometry, immunohistochemistry, etc). For this reason, the HIV Prevention Trial Network sponsored the HPTN 056 study "Characterization of Baseline Mucosal Indices of Injury and Inflammation in Men For Use in Rectal Microbicide Trials" conducted at UCLA. The lessons learned from the HPTN 056 trial have guided the selection of parameters to be included in Project 4. As these are assays in development and clinical relevance remains to be defined, these will not be safety indices but secondary endpoints. The rationale for selecting each of these endpoints is further described in Section 2.1.2.

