#### **7.3.1 Emergency Unblinding Procedures**

Subjects may be unblinded for safety or medical treatment purposes. The investigator must, whenever possible, phone the study's designated SMC medical monitor to unblind the code. The medical monitor will notify the investigator and sponsor that a subject was unblinded without revealing what the treatment assignment was. Appropriate documentation must be submitted to the investigator and CONRAD within 3 working days of unblinding. Any subject that is unblinded must be discontinued from the study.

The Emergency Unblinding Code specifying the subject's treatment code is located on the drug label. Only in case of medical emergency, can the investigator break the masking code by scratching off the unmasking cover. This label is affixed to the drug label source.

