## **7.6 Statistical Procedures for Analysis of Mucosal Damage Parameters**

The associations of six sets of mucosal parameters with the use of study product will be examined as a secondary objective. Four of these parameter sets (Histopathology, Cell Phenotype, Cytokine profile, Fecal Calprotectin) are collected three times per patient: at baseline, post-Treatment 1 and post-Treatment 2. The remaining two sets (Epithelial Sloughing and Immunoglobulins) are four times per patient: at baseline, pre- and post-Treatment 1, and post-Treatment 2. For all six parameter panels, the main question of interest is whether the three treatment groups (placebo, low, and high) have systematically different mucosal damage parameters post-Treatment 1 and post-Treatment 2. In particular, we will be assessing whether either of the UC-781 treatment groups have evidence of more mucosal damage than the placebo group. As described below, at least four of the six parameter sets should be stable and sensitive enough that important clinical differences would be statistically detectable.

As subjects will be randomized to the three treatment groups, systematic baseline differences are not expected; however, due to the relatively small study size, it is quite likely that many parameters will be quite different between treatment groups at baseline. All analyses will therefore be conducted both with and without controlling for baseline measurements. For continuous measures, it is well-known that controlling for baseline differences in regression models is more powerful than analyzing changes from baseline.

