### **RISKS FROM UC-781 OR PLACEBO**

Minimal local irritation and little or no systemic adverse effects are expected with the use of UC-781 gel per rectum at the concentration proposed in this study. However, this formulation of UC-781 gel has not been tested rectally in humans previously. Therefore, the risks of treatment are not known and careful monitoring for adverse effects is planned. A summary of AEs reported to date in clinical studies of vaginal UC-781 and related compounds, which may be relevant for the use of the UC-781 rectally is provided in section 1.2.

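### Imputation models built on HPTN 056 rather than on this trial's data would shrink any true UC-781 versus placebo difference in the secondary mucosal measures

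*Protocol*

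**What the plan says.** Section 7.10 expects gaps from missed visits, loss to follow-up and incomplete assessments. To fill them, and "to be able to perform intent to treat analysis on the outcomes, multiple imputation" is chosen, run in the SAS MI procedure or IVEware. On the source of the models, the section rules that "imputation model building will be based wherever possible on the data from HPTN 056". The reason it gives for this choice is to keep model construction separate from the results of this trial: "In order to construct these models independently of the data from the current study".

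Section 1.1 gives the title of HPTN 056 as "Characterization of Baseline Mucosal Indices of Injury and Inflammation in Men For Use in Rectal Microbicide Trials". Section 8.3 says that "this formulation of UC-781 gel has not been tested rectally in humans previously". The Schema defines the population of this trial as "HIV negative men and women with a history of RAI".

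Section 7.6 sets the question for the secondary mucosal parameters: "whether either of the UC-781 treatment groups have evidence of more mucosal damage than the placebo group". Continuous parameters are analysed by ANCOVA of the post-treatment value on baseline and treatment group, with placebo as reference. Section 3.5 does not replace participants who withdraw after dosing, so their gaps remain to be imputed.

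**The concern.** An imputation model should contain the variable whose effect the analysis will test. Here that variable is treatment arm. HPTN 056 had no UC-781 arm from which an arm effect could be estimated, and 7.10 says the models are to be built without the trial data that could supply one. A missing value in a UC-781 participant would then be drawn as though that participant had used no gel, and likewise in a placebo participant. The filled-in values look alike across arms whatever the gel does, and they dilute the contrast that Section 7.6 sets out to estimate.

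The stake is the mucosal comparison in a first rectal study of this gel. Real damage would look smaller and be harder to detect. A real benefit in any measure imputed the same way would also look smaller. In addition, the source study was in men, whereas this trial enrols men and women.

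**Working it through.** Section 7.10 states no missing rate, effect size or attenuation, so there is no figure of the plan's own to reproduce.

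**Step 1. Which measures are reached.** Section 7.6 cites HPTN 056 data for histopathology, cell phenotype, cytokines and immunoglobulins. For sloughing and calprotectin it cites other sources. The words about basing models on HPTN 056 where possible therefore bite on the measures that study collected.

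**Step 2. Algebra.** Let μ be the mean of an unexposed participant given baseline, δ the true UC-781 minus placebo difference, and g any shift from the placebo gel or procedures. Let a and p be the shares of post-treatment values missing at random in the UC-781 and placebo arms. Imputed values have mean μ in both arms.

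- UC-781 arm mean: (1 − a)(μ + g + δ) + aμ
- Placebo arm mean: (1 − p)(μ + g) + pμ
- Difference: (1 − a)δ + (p − a)g

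With equal missingness, or with g = 0, the expected difference is (1 − a)δ. For 12 per arm:

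- 0 missing: 12/12 = 100% of δ kept
- 1 missing: 11/12 = 92%
- 2 missing: 10/12 = 83%
- 3 missing: 9/12 = 75%

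**Step 3. Simulation.** One UC-781 arm against placebo, 12 each (Schema), with ANCOVA on baseline (Section 7.6). Missingness was completely at random and equal in both arms, with 10 imputations from an untreated model, Rubin's rules and 1,500 trials per setting. Correlations of 0.5 and 0.8 reflect Section 7.6 (around 0.5 for CCR5 measures, 0.7 to 0.9 for the stable phenotype measures). A true harm of 1 SD, the missing counts and a two-sided 0.05 test are assumptions.

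| Correlation | Missing per arm | Share of δ kept, imputed | Share of δ kept, observed values only | P(p<0.05), imputed | P(p<0.05), observed values only |
|---|---|---|---|---|---|
| 0.5 | 0 | 100% | 100% | 0.75 | 0.75 |
| 0.5 | 1 | 91% | 99% | 0.63 | 0.70 |
| 0.5 | 2 | 84% | 101% | 0.49 | 0.65 |
| 0.5 | 3 | 75% | 100% | 0.34 | 0.62 |
| 0.8 | 0 | 101% | 101% | 0.97 | 0.97 |
| 0.8 | 1 | 93% | 101% | 0.93 | 0.95 |
| 0.8 | 2 | 84% | 101% | 0.82 | 0.92 |
| 0.8 | 3 | 75% | 100% | 0.69 | 0.89 |

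The attenuation follows 1 − a. ANCOVA on observed values recovers the true difference when data are missing at random in this way.

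**Step 4. A second setting.** Assume a harm of 0.90 SD with values missing in the active arm only. The formula gives 0.90 × 11/12 = 0.825, 0.90 × 10/12 = 0.75 and 0.90 × 9/12 = 0.675 SD. Simulation gave 0.83, 0.76 and 0.67 SD, against about 0.90 SD for ANCOVA on observed values.

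**Step 5. If HPTN 056 supplies only the model form.** Fitting an arm-free model to the pooled trial data kept 91%, 83% and 74% of the difference with 1, 2 and 3 missing at correlation 0.5. That is about the same shrinkage, so what matters is whether arm is in the model.

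**The case against.** The strongest reply is that 7.10 speaks of model building, qualified by what is possible, and names software that ordinarily estimates its parameters from the data set being imputed. On that reading HPTN 056 only fixes predictors and transformations in advance, and arm, which cannot come from HPTN 056, may still be added. The text never says in so many words that arm is left out. This reading is fair, but it removes the bias only if an arm term is included and fitted to trial data (Step 5). The section does not say so, and its stated aim of independence from the current data points the other way.

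Three further points stand.

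- **Reach.** Post-dose specimens at Visit 3 are taken about 30 minutes after the dose (Section 5.3.2), and participants withdrawn before dosing are replaced. The gaps should therefore fall mainly at Visit 5.
- **Participants not cleared for Stage 2.** They never take the 7-day course, so an untreated value may be close to their actual state. This does not justify using untreated values for participants who did take the gel.
- **Size.** With 1 of 12 missing and correlation 0.8, the chance of p<0.05 moves only from 0.95 to 0.93. The simulations cover continuous measures only, whereas sloughing and histopathology are to be read on binary or ordinal scales.

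A reader might infer that the missing values will mostly belong to participants stopped for safety, for example because "Any subject that is unblinded must be discontinued from the study". The documents do not support that: 7.10 names missed visits, loss to follow-up and noncompliance, and the attenuation shown does not depend on it. If harmed participants were selectively missing, ANCOVA on observed values would be biased as well.

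**Conclusion.** The point holds for the secondary mucosal measures that HPTN 056 collected. Followed as written, 7.10 pulls any true UC-781 versus placebo difference toward zero by about the share of values missing: 0% with none missing, about 8%, 17% and 25% with 1, 2 and 3 of 12. These figures assume missingness unrelated to outcome and either equal missing shares or no shift from placebo gel or procedures. Unequal missingness combined with such a shift adds the term (p − a)g, which can act in either direction. The missing counts and effect sizes are assumptions, not protocol figures.

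A stronger reading, that the rule biases the trial toward declaring the gel safe, goes too far. The primary safety measure is the frequency of Grade 2 or higher adverse events (Section 7.4), which this rule does not affect. Section 1.1 calls the mucosal assays secondary endpoints rather than safety indices, and no safety decision is tied to these tests. Nor does the point show that an analysis of observed values must replace multiple imputation as the main analysis; that is a debatable choice.

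**What to change.** Replace the last sentence of Section 7.10. The new text should state that:

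- the imputation model is fitted to this trial's data and includes treatment arm, baseline value and sex, plus the other post-dose visit where available;
- HPTN 056 is used only to pre-specify transformations or auxiliary variables, which keeps those choices free of the trial results;
- the ANCOVA on observed values is reported alongside the imputed analysis.

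This is a wording change with no effect on visits or sample size. The cost is somewhat larger imputation variance, because only 36 participants inform the model.
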